### Other measures and questionnaires

During the hospital admission's final eligibility assessment, we will conduct the M.I.N.I-S International Neuropsychiatric Interview [48] to identify potential comorbid psychiatric disorders. Additionally, a self-developed questionnaire will gather information on demographic and clinical parameters. We will also maintain a comprehensive and detailed record of all medications, including antibiotics and any supplements, taken before and throughout the study.

The nursing staff at the hospital unit recurrently measures the participant's weight, while their height is measured during the initial visit. From these data points, we will systematically calculate BMI. In addition to monitoring their autonomic nervous system activity during the TSST, the wearable device will also track their physical activity during both study visits.

Participants will complete self-reported questionnaires on four occasions during the study: on the first, second, and third study visits and three weeks into the intervention between the first and second visits. Changes in eating disorder symptoms will be evaluated using the Eating Disorder Examination Questionnaire (EDE-Q) [49]. Additionally, restrained, emotional, and external eating behavior will be assessed by the Dutch Eating Behavior Questionnaire (DEBQ) [50]. 'Hedonic hunger' is measured through the Power of Food Scale (PFS) [51]. Furthermore, depressive symptoms, anxiety symptoms, affect, and stress will be assessed using the Depression, Anxiety, Stress Scales (DASS) [52], the Positive and Negative Affect Schedule (PANAS) [53], and the Perceived Stress Scale (PSS) [54]. Gastrointestinal complaints are scored using the Gastrointestinal Symptom Rating Scale (GSRS) [55] and the Rome IV questionnaire for functional gastrointestinal disorders [56].

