### Interventions and concomitant care

We will efficiently deliver SCFAs to the large intestine by utilizing pH-dependent CDCs to mimic the process of dietary fiber fermentation in the colon, as done previously [19]. Participants will consume capsules of a mixture of SCFAs spread at four intervals throughout the day. The SCFA mixture contains acetate, propionate, and butyrate in a ratio of 60:20:20, and the total daily amount of SCFAs is equivalent to the fermentation of 10 g of arabinoxylan oligosaccharides [38]. Microcrystalline cellulose, not absorbed in the gastrointestinal tract, will be included in the same type of CDCs to serve as a placebo. The nursing staff will distribute the capsules to the participants individually, supervise their intake, and monitor adherence by capsule count. Although adverse effects are not expected [19], these will be documented. Participation will be discontinued if the patient exhibits a high medical or psychiatric risk requiring priority or fails to adhere to the consumption of the intervention substances (taking less than 80% of capsules) or to the study procedures.

Participants in both groups will receive treatment as usual, consisting of an inpatient psychotherapeutic program of 12 weeks focusing on nutritional rehabilitation. We will closely monitor the use of other medications throughout the study. However, such usage will not lead to the termination of the trial intervention. After undergoing the intervention and post-intervention visit, if any participant decides to leave the residential program early, we will still aim for a follow-up visit to take place at the hospital.

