## Outcomes

### Primary and secondary outcomes

The primary outcome of this study focuses on the salivary cortisol response to acute laboratory stress. We will examine the change in cortisol levels within and between SCFAs and placebo groups. Crucial secondary outcomes encompass the participants' food choices and nutritional status (BMI). All other measures delineated in the subsequent sections serve as secondary outcome measures. See Table 1 for an overview of scheduled assessments.

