### Statistical analysis

#### Statistical methods for primary and secondary outcomes

The primary and secondary outcome variables will be analyzed using linear mixed models with “group” (placebo or SCFAs) as a between-subject factor and “visit” (pre- or postintervention) and, where appropriate, “timepoint” (measurement point within each visit) as within-subject factors. The group-by-visit and the group-by-visit-by-timepoint interaction effects constitute the principal effects of interest. If participants fail to exhibit an elevated cortisol stress response following stress induction, we will exclude their data from the analysis. To investigate the effect of the SCFAs intervention on treatment response, we will further control for BMI by including changes in BMI between visits 1, 2, and 3 in the linear mixed model as a continuous covariate. To investigate whether the changes in circulating SCFAs levels are mediated by the changes in the cortisol stress response to our stressor, we will pool all stress responders and enter the change in SCFA levels (post-intervention—pre-intervention) into the linear mixed model as a continuous covariate, including its interaction with visit, while omitting the group variable. The chosen significance level is alpha = 0.05. Follow-up planned contrasts will be conducted if there is a significant interaction effect and will be corrected for multiple testing comparisons using step-down Bonferroni (Holm) adjustment. Data of the intervention group will be further exploratively analyzed using linear mixed models with restrictive type AN and binge/purge type AN as “patient group,” investigating differences between the intervention of SCFAs between subtypes of patients with AN. In addition, we will enter the changes in questionnaires (baseline, post-intervention) into a linear mixed model as continuous covariates to investigate in an explorative way whether these changes (e.g., in AN severity, affect changes, subjective stress, etc.) are mediated by the changes in SCFAs levels and microbiota composition.

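### The BMI model has only a pre and a post occasion, so ward weights taken between visits go unused: precision is lost when week 6 is missing, and selection bias is possible in a direction the protocol cannot settle

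*Protocol article*

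**What the plan says.** - **Role of BMI** (Primary and secondary outcomes): "Crucial secondary outcomes encompass the participants' food choices and nutritional status (BMI"), ahead of all other secondary measures.
- **Measurement** (Other measures and questionnaires): "The nursing staff at the hospital unit recurrently measures" each patient's weight, with height taken once, at the first visit. It continues: "From these data points, we will systematically calculate BMI". The weighing frequency is not given.
- **Model** (Statistical methods for primary and secondary outcomes): "The primary and secondary outcome variables will be analyzed using linear mixed models with" group as the between-subject factor. The visit factor is "pre- or postintervention) and, where appropriate", a timepoint factor is added, defined as "measurement point within each visit) as within-subject factors". The effects of main interest are the interactions of group with visit and with visit and timepoint. BMI change across visits 1 to 3 appears in this section only as a covariate.
- **Stopping** (Interventions and concomitant care): "Participation will be discontinued if the patient exhibits a high medical or psychiatric risk requiring priority", or for taking under 80% of capsules or not following procedures. Follow-up of early leavers is described only for those who leave after the post-intervention visit.
- **Setting and planning rate**: the inpatient programme lasts 12 weeks (Study design and setting), and 15% dropout is planned for (Sample size).

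**The concern.** The article describes serial weights but fixes a model that can use two of them. Consider a patient who leaves the ward in week 4. She has several dated weights that show how she was gaining, yet the model sees only her baseline. In effect it predicts her week-6 BMI from baseline alone, using the patients who stayed.

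Two things are at stake. The first is precision in an outcome the investigators call crucial. The second is selection. In malnourished inpatients, poor gain may plausibly accompany the medical risk, non-adherence or departure that ends participation; this is an inference, not something the article states. If so, the missing week-6 values are related to weights that were recorded but are left out of the model.

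**Working it through.** **1. The plan's own figure.** There is no power statement for BMI. The general sensitivity figure is 80% power for f = 0.16 with 80 patients in a 2 × 2 mixed design. With an assumed correlation of 0.5 between visits, λ = f²·N·m/(1 − ρ) = 0.0256 × 80 × 2 / 0.5 = 8.19 on 1 and 78 df. This gives 80.7%, so the figure is reproduced. It does not bear on the choice of BMI occasions.

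**2. What the model can use.** Between-visit weights are neither a pre nor a post value, and they are not a point within a visit. A patient without a week-6 value therefore supplies baseline only.

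**3. Precision.** Of 92 patients, 92 × 0.85 = 78.2 have a week-6 value if all the planned 15% dropout means a missing weight. The standard error ratio is √(92/78.2) = 1.085.

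Simulation A checks this with 3,000 trials per scenario, 92 patients and about 15% stopping, with last weights at weeks 2 to 5. Assumed inputs: true difference in BMI change 0.50 kg/m², baseline SD 1.2, mean gain 0.25 per week, SD of weekly slope 0.12, error SD 0.2.
- SD of six-week change = √((6 × 0.12)² + 2 × 0.2²) = √0.598 = 0.774.
- Expected SE with 46 per arm: 0.774 × √(2/46) = 0.161.
- Expected SE with 39.1 per arm: 0.774 × √(2/39.1) = 0.175.
- Simulated SEs with random stopping: 0.162 with no dropout, 0.175 for the two-visit model, 0.165 with weekly weights.

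**4. Bias.** Mean estimates from Simulation A, true value 0.50, both models fitted by likelihood:

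| Stopping mechanism | Two-visit | All weekly weights |
|---|---|---|
| Unrelated to gain | 0.50 | 0.50 |
| Low gainers, equal rates in both arms | 0.50 | 0.50 |
| Low gainers, SCFA arm only | 0.61 | 0.51 |
| Low gainers, placebo arm only | 0.39 | 0.50 |
| Low gainers on placebo, high gainers on SCFA | 0.28 | 0.50 |

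In every row the standard error is 0.174 to 0.176 for the two-visit model and 0.162 to 0.167 with weekly weights.

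**5. One absolute rule in both arms.** The second row of the table equalises stopping rates between arms. Simulation B instead lets stopping depend on a patient's actual gain to week 3, by the same rule in each arm. It has 46 per arm, true effect 0.50, SD of gain 0.9 and residual SD 0.15, all assumed. With a real benefit, more placebo than SCFA patients then fall in the range where stopping is likely.
- At about 13–17% stopping the two-visit estimate is 0.43 to 0.48, depending on how steep the rule is. The shift of 0.02 to 0.07 compares with an SE of about 0.9 × √(2/39.1) = 0.20.
- At about 25% stopping, beyond the planned rate, the estimate is about 0.43.
- When stopping depends on gain relative to the patient's own arm mean, the estimate returns to 0.50–0.51.
- Using weights up to stopping gives about 0.50 under both rules.

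**The case against.** - **A reader might infer that the BMI effect is simply attenuated.** The article does not support that. It says nothing about how stopping relates to gain, and the same two-visit model is unbiased, attenuated or inflated depending on that relation. There is an argument for attenuation: blinded staff can react only to a patient's actual weight course, which favours the single absolute rule. That makes attenuation plausible if SCFAs work, but does not establish it. Tolerability or adherence could differ by arm and push the estimate either way.
- **A reader might also infer that anyone who stops before week 6 has no post-baseline BMI.** This goes too far. The programme runs 12 weeks, so a patient who stops capsules may still be weighed on the ward at week 6, and that weight fits the post level directly. The article does not say whether it would be used.
- **One generic sentence in a condensed article covers many outcomes, and a pre/post contrast is not an error in itself.** Both points are fair. Detailed handling of early stoppers may be in a fuller document and is not held against the article. What remains is that the article does fix the factor levels, and they do not match the serial BMI data it describes.
- **The simulated gain is linear.** This stands as a limit on the simulations, and as a reason not to force a linear time trend in the replacement model.

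**Conclusion.** The concern holds as a modest, inexpensive improvement. The stated BMI model leaves already-collected ward weights unused, and a patient without a week-6 weight contributes baseline only. The cost that does not depend on the dropout mechanism is a standard error about 8% wider, if 15% of week-6 weights are missing. That percentage is the planning rate for dropout overall, so it is an upper figure to the extent that stoppers stay on the ward and their week-6 weight is used.

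The contrast is also open to selection bias: toward zero under one absolute rule with a true benefit, either way if the relation to gain differs by arm, and none if stopping is unrelated to gain or related equally around each arm's mean. Near the planned dropout rate, the single-rule shift in the settings tried was at most about a third of a standard error (0.07/0.20). Arm-specific mechanisms gave larger shifts. All bias sizes rest on assumed BMI inputs and weekly weighing.

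**What to change.** In the statistical methods section, give BMI its own model: a longitudinal mixed model on all dated ward weights from baseline to week 6, in all randomised patients. Enter time as categorical weeks or a flexible function, not a forced straight line, with a group-by-time interaction and a stated within-patient covariance structure. Estimate the week-6 group difference from that model.

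State that weights up to stopping are included. State also that routine ward weights, week 6 among them, are used for patients who stop capsules but stay on the ward, where consent allows. Weights between weeks 6 and 12 are not needed for this estimate.

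In Simulation A this model brought the standard error back to 0.162–0.167 and the estimate to 0.50–0.51 in every scenario. It relies on stopping being explained by the recorded weights. The cost is an extract of ward weights, slightly more modelling, and consent wording that covers routine weights after discontinuation. No extra visit, measurement or patient is required.

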### Statistical analysis

#### Statistical methods for primary and secondary outcomes

The primary and secondary outcome variables will be analyzed using linear mixed models with “group” (placebo or SCFAs) as a between-subject factor and “visit” (pre- or postintervention) and, where appropriate, “timepoint” (measurement point within each visit) as within-subject factors. The group-by-visit and the group-by-visit-by-timepoint interaction effects constitute the principal effects of interest. If participants fail to exhibit an elevated cortisol stress response following stress induction, we will exclude their data from the analysis. To investigate the effect of the SCFAs intervention on treatment response, we will further control for BMI by including changes in BMI between visits 1, 2, and 3 in the linear mixed model as a continuous covariate. To investigate whether the changes in circulating SCFAs levels are mediated by the changes in the cortisol stress response to our stressor, we will pool all stress responders and enter the change in SCFA levels (post-intervention—pre-intervention) into the linear mixed model as a continuous covariate, including its interaction with visit, while omitting the group variable. The chosen significance level is alpha = 0.05. Follow-up planned contrasts will be conducted if there is a significant interaction effect and will be corrected for multiple testing comparisons using step-down Bonferroni (Holm) adjustment. Data of the intervention group will be further exploratively analyzed using linear mixed models with restrictive type AN and binge/purge type AN as “patient group,” investigating differences between the intervention of SCFAs between subtypes of patients with AN. In addition, we will enter the changes in questionnaires (baseline, post-intervention) into a linear mixed model as continuous covariates to investigate in an explorative way whether these changes (e.g., in AN severity, affect changes, subjective stress, etc.) are mediated by the changes in SCFAs levels and microbiota composition.

To examine restrictive food choice behavior using the FCT, we will use mixed effects logistic regression models on the binary choice data, where the participant's choice (selection of the trial-unique food item over the reference item) is the dependent variable, and z-scored healthiness and tastiness ratings are entered as independent variables. To assess self-control, we first categorize the trials as to whether they present a conflict between healthiness and tastiness ratings (food items rated tasty and unhealthy or non-tasty and healthy). In these trials, “self-control” is used when choosing healthy but non-tasty food or not choosing tasty but unhealthy food. Trials that elicit neutral responses are excluded. The proportion of trials with an opportunity for self-control and use versus nonuse of self-control will be modeled using mixed effects logistic regression.

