### Study design and setting

This study is a monocentric, randomized, triple-blind, placebo-controlled trial with two parallel arms. Participants in both groups will receive concomitant treatment as usual, consisting of an inpatient psychotherapeutic program of 12 weeks focusing on nutritional rehabilitation. Using a block randomization method, we will randomly assign participants to the placebo or SCFA group with a 1:1 allocation ratio. The total duration of the study is 12 weeks, including a pre-intervention baseline visit, which takes place within the first week of hospitalization, a post-intervention visit at six weeks, and a follow-up visit at 12 weeks. The study will be conducted at the Leuven University Psychiatric Hospital (UPC Z.Org), Belgium.

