### Sample size

Based on our previous work [19], we calculated, using the General Linear Multivariate Model Power and Sample Size software (GLIMMPSE), that a total sample size of 70 participants (n = 35 per treatment arm) yields sufficient power (80%) to detect the previously found effect of SCFAs on the cortisol response to an acute stress paradigm. Given that no information is available to calculate the effects of SCFAs on stress-induced cortisol response in patients with AN where greater variability might be present, we increased the sample size to 80 participants (n = 40 per arm). Based on a sensitivity power calculation (G*Power 3.1.9.2 software), 40 participants per arm would enable us to achieve 80% power to detect a small effect (Cohen's f = 0.16) in a within-between 2 (“visit”, baseline vs. post-intervention) × 2 (“treatment”, placebo vs. SCFA) mixed ANOVA model. Taking into consideration a 15% risk of dropout, we aim to recruit 92 individuals in total.

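### The primary cortisol model is valid but does not adjust for the baseline response, which costs about 25% in variance if the pre-post correlation is 0.5, and more or less at other values.

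*Protocol article*

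**What the plan says.** The section on statistical methods for primary and secondary outcomes describes a linear mixed model with group ("placebo or SCFAs) as a between-subject factor" and with visit and, where appropriate, timepoint as within-subject factors. It then says: "The group-by-visit and the group-by-visit-by-timepoint interaction effects constitute the principal effects of interest". The pre-intervention values are therefore a level of the outcome.

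The covariate named for the treatment-effect analysis is BMI change ("including changes in BMI between visits 1, 2, and 3 in the linear mixed model as a continuous covariate"). Neither baseline cortisol as a covariate nor an equal baseline mean is mentioned. On the outcome, the protocol says: "The primary outcome of this study focuses on the salivary cortisol response to acute laboratory stress". The stress test is done at the baseline and post-intervention visits, and participants are randomised "with a 1:1 allocation ratio".

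The Sample size section powers the same kind of contrast, visit by treatment in a 2 × 2 mixed ANOVA: "40 participants per arm would enable us to achieve 80% power to detect a small effect (Cohen's f = 0.16"). It gives no pre-post correlation. The same section raises the total from 70 to 80 because variability may be greater in anorexia nervosa.

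**The concern.** Baseline cortisol is measured before the intervention in a randomised trial, so the expected difference between arms at that visit is zero. A model that estimates this difference freely and subtracts it from the post-intervention difference carries the chance imbalance at baseline into the treatment effect. Adjusting for baseline, or fixing the baseline means as equal, removes part of that noise at no cost.

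Precision is at stake, not validity. The plan adds ten patients as protection against greater variability. The analysis model may give up more precision than those ten patients buy, depending on a correlation that the protocol does not report.

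**Working it through.** **Inputs from the protocol.** 40 per arm (N = 80), 80% power, f = 0.16, a 2 × 2 mixed model and alpha 0.05 ("The chosen significance level is alpha = 0.05"). **Assumed.** Two-sided testing, equal pre and post variance s², complete data, and ρ as stated at each step.

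**1. Reproduce the plan's figure.** For the within-between interaction, λ = f²·N·m/(1−ρ) with m = 2 and df 1 and 78. At ρ = 0.5, λ = 0.0256 × 80 × 2 / 0.5 = 8.19.

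- Power is 0.807 at f = 0.16, and 80% power is reached at f = 0.159. The stated figure reproduces.
- At ρ = 0.4 power is 0.733 and at ρ = 0.6 it is 0.885, so neither reproduces it.
- Allowing for rounding of f, the implied ρ is 0.46 to 0.52.

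**2. Equivalence with change.** On one simulated complete data set of 80, the mixed-model group-by-visit estimate and SE were 0.6918 and 0.1875. The comparison of change gave the same two values. The baseline-adjusted SE was 0.1731.

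**3. Variance.** Per participant, the variance is 2(1−ρ)s² for change and (1−ρ²)s² with baseline adjustment. The ratio is (1+ρ)/2, so the loss is (1−ρ)/2.

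**4. Power with 40 per arm.** The difference is held at 0.64 SD, which is √8.19 × √(4/80).

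| ρ | Variance ratio | Loss | Power, change | Power, adjusted |
|---|---|---|---|---|
| 0.3 | 0.65 | 35% | 0.666 | 0.842 |
| 0.5 | 0.75 | 25% | 0.807 | 0.904 |
| 0.7 | 0.85 | 15% | 0.954 | 0.977 |
| 0.9 | 0.95 | 5% | 1.00 | 1.00 |

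At ρ = 0.5 the difference detectable with 80% power falls from 0.63 to 0.55 SD. Adjusted analysis of 80 × 0.75 = 60 participants matches change analysis of 80. In 5,000 simulated trials at ρ = 0.5 the variance ratio was 0.77 and power was 0.81 against 0.90. The implied ρ of 0.46 to 0.52 gives a loss of 24% to 27%.

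**5. Against the 70-to-80 margin.** Setting 80(1+ρ)/2 = 70 gives ρ = 0.75. The gain exceeds the ten-patient margin only below that value.

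**6. Effect of excluding cortisol non-responders.** The protocol drops participants without an elevated cortisol response but does not say at which visit this is judged. Assumptions: ρ = 0.5, true effect −0.634 SD, mean response 1 SD, and non-response meaning a response of zero or below.

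- *Judged at baseline only:* the arms stay comparable at baseline and both estimators are unbiased. With v the baseline variance after truncation, the ratio is 0.75/(0.75 + 0.25v). It is about 0.83 here, and 0.80 to 0.86 for mean responses from 1.5 down to 0.5 SD.
- *Judged at either visit:* the retained arms differ at baseline by 0.09 SD. Change analysis estimates −0.46 and baseline adjustment −0.40. Both are attenuated, the adjusted one more so.

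**The case against.** The strongest reply is that nothing here is wrong. The contrast is valid under randomisation, and the power statement was made for the same kind of contrast. Both points stand. A reader might infer that the trial is underpowered against its claim, or that the treatment estimate is biased by the lack of adjustment. The documents support neither.

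A reader might also take the loss of a quarter as a fact about this trial. It is not. No correlation for the cortisol response is given, ρ = 0.5 is back-solved from a sensitivity calculation without timepoints, and the calculation behind the 70 participants rests on inputs not shown. The power figures are for one two-visit contrast, not for the interaction with timepoint over eight saliva samples. Nor can the size be carried over to BMI: if its correlation were 0.9, the loss would be 5%.

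The exclusion of non-responders is a real objection. If response at the post-intervention visit counts, selection follows randomisation and can depend on treatment, so the equal-baseline premise fails in the analysed set. This limits where the fix may be applied but does not remove the point.

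Lastly, an unseen analysis plan might constrain the baseline. But the article does state the factors, the target effects and a covariate, and on its natural reading the group difference at baseline is free.

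**Conclusion.** The point holds as one of efficiency. The stated model forgoes an improvement that uses data the trial already collects. The loss in variance is (1−ρ)/2: 25% at the ρ of 0.5 implied by the sensitivity calculation, 35% at 0.3, 15% at 0.7 and 5% at 0.9. At ρ = 0.5 this is 80% against 90% power for a single two-visit contrast. It outweighs the increase from 70 to 80 only if ρ is below about 0.75.

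These figures assume complete data, equal variances at the two visits, and an analysis set not selected on post-intervention cortisol. With missing post-intervention data, the equivalence with change is not exact. The change is worth making, but the planned analysis would not be invalid without it.

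**What to change.** In the statistical methods section, specify the mixed model with no group difference at the pre-intervention visit. Keep the visit and timepoint terms, and the group and group-by-timepoint terms at the post-intervention visit. A similar but not identical alternative is to model the post-intervention response with the participant's baseline response as a covariate. The two differ when there are several timepoints or missing data.

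Apply the model to all randomised participants, or to a set defined only by the baseline stress response, and say which. The same form can be used for other outcomes measured at baseline, where the gain may be small if the correlation is high. State the assumed pre-post correlation in the Sample size section.

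The model itself takes a sentence or two, with no new data and no extra participants. The responder rule must be settled at the same time, because the equal-baseline constraint depends on it.

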### Measurements related to the TSST

#### Neuroendocrine measures

To measure the adrenocortical stress response during the TSST, we will collect eight saliva and four blood samples at regular intervals before, during, and after stress induction (see Fig. 3). Saliva samples will be obtained using synthetic Salivette devices and will be used to determine salivary cortisol and alpha-amylase (sAA) levels. Blood samples will be collected through an IV catheter in EDTA tubes to measure ACTH levels. After collection, all samples will be centrifuged and stored at − 80 °C until analysis by ELISA. Additionally, the participants' menstrual cycle phase and any use of hormonal contraceptives will be noted for its effect on the salivary cortisol response to acute stress.

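### Two interactions are named as principal for the single primary outcome, with no rule on which one decides: type I error can reach 9.75%, one of the two need not measure stress reactivity, and the 2 x 2 power figure covers only that one

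*Protocol article*

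**What the plan says.** Under Primary and secondary outcomes: "The primary outcome of this study focuses on the salivary cortisol response to acute laboratory stress". Under Neuroendocrine measures, the sampling at each stress test is: "we will collect eight saliva and four blood samples at regular intervals before, during, and after stress induction".

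Under Statistical methods for primary and secondary outcomes, all primary and secondary variables go into linear mixed models with group, visit and, for outcomes where it applies, timepoint ("measurement point within each visit) as within-subject factors"). The same section then states:

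- "The group-by-visit and the group-by-visit-by-timepoint interaction effects constitute the principal effects of interest"
- "The chosen significance level is alpha = 0.05"
- "Follow-up planned contrasts will be conducted if there is a significant interaction effect"; these contrasts "will be corrected for multiple testing comparisons using step-down Bonferroni (Holm) adjustment"

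The Sample size section gives two calculations. The first, in GLIMMPSE, finds 70 participants sufficient for 80% power to detect the effect on the cortisol response seen in the group's earlier study; it does not name the contrast tested. The second, in G*Power, is a sensitivity calculation: "40 participants per arm would enable us to achieve 80% power to detect a small effect", with Cohen's f = 0.16, in a visit-by-treatment 2 x 2 mixed ANOVA that has no timepoint factor.

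**The concern.** Three things follow from naming two principal interactions for one primary outcome.

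- **Error rate.** Nothing ranks the two terms, splits alpha between them or says which one decides. Follow-up is triggered by a significant interaction, without saying which. That leaves room for two chances of success at 0.05 each.
- **What is tested.** In a model on the individual samples, with effects averaged over timepoints, group-by-visit compares the arms on the change in mean cortisol across all samples, including those taken before the stressor. A change in basal cortisol with an unchanged stress response would be positive on this term. Only the term involving timepoint concerns the shape of the response.
- **Power.** The 2 x 2 calculation matches group-by-visit. It says nothing about the three-way term, which is the one closer to the stated outcome.

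At stake is whether a positive primary result can be read as an effect on stress reactivity at the stated 5% level.

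**Working it through.** **Inputs from the protocol.** One primary outcome; two principal interactions; alpha 0.05; 8 saliva samples per visit; 2 visits; 40 per arm (N = 80); f = 0.16; stated power 80%. The correlation between visits is not given. I assume 0.5, which reproduces the stated power, and show a range.

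**1. Reproducing the stated power.** For the within-between interaction with m = 2 visits, the noncentrality is lambda = f^2 x N x m / (1 - rho), with 1 and N - 2 degrees of freedom. At rho = 0.5, lambda = 0.0256 x 80 x 2 / 0.5 = 8.192, and power on (1, 78) df is 80.7%. The stated 80% is confirmed for the two-way test. At rho = 0, 0.3 and 0.7 the power is 51.6%, 66.6% and 95.4%. The GLIMMPSE figure cannot be checked because its inputs are not given.

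**2. Type I error.**

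| Decision rule for cortisol | Type I error |
|---|---|
| Either interaction suffices, each at 0.05 | 1 - 0.95^2 = 9.75% (Bonferroni bound 10%) |
| Only the three-way term decides | 5% |
| Both kept, each at 0.025 | at most 5% |

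A simulation of null trials (8 timepoints, 2 visits, 40 per arm, 20,000 trials, multivariate test for the three-way term) gave 9.7% for the first rule under compound symmetry and 9.5% under a first-order autoregressive correlation of 0.8.

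Under the third rule, two-way power at f = 0.16 and rho = 0.5 falls to 71.7%, and 96 completers would be needed for 80%.

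**3. The two interactions detect different things.** The effect shapes below are assumed. Each simulation used 40 per arm and 4,000 trials; ranges cover the two correlation structures.

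| True effect | Group-by-visit power | Three-way power |
|---|---|---|
| Flat shift over all 8 samples, f = 0.16 on the visit mean | 80% | 4 to 5% |
| Same standardized difference at the peak samples, smaller or none at the others | 30 to 32% | 83 to 90% |

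A flat shift is what a basal change would look like. The two-way test finds it; the three-way test stays near its alpha.

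**4. What baseline adjustment would add.** With equal variances at the two visits, the variance of the arm difference is proportional to 2(1 - rho) for change scores and to 1 - rho^2 after adjustment for baseline. The ratio is (1 + rho)/2, so lambda is divided by that factor. With f = 0.16 and N = 80 held fixed:

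| rho | lambda, change | power | (1 + rho)/2 | lambda, adjusted | power |
|---|---|---|---|---|---|
| 0.3 | 5.85 | 67% | 0.65 | 9.00 | 84% |
| 0.5 | 8.19 | 81% | 0.75 | 10.92 | 90% |
| 0.7 | 13.65 | 95% | 0.85 | 16.06 | 98% |

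The adjusted test uses (1, 77) df.

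**The case against.** The strongest reply is that the sentence covers every primary and secondary outcome and that timepoint enters only for some of them. It can then be read term by term: the two-way interaction for outcomes measured once per visit, such as BMI, and the three-way for repeatedly sampled ones, such as cortisol. Cortisol would have one decisive test, at 5%. This reading is possible, and no sentence says that either interaction alone is enough. A reader might therefore infer that type I error simply is about 10%; the documents support that only as the worst case. But the text joins the two terms without assigning them to outcomes, so the ambiguity remains. On the term-by-term reading, the decisive cortisol test would be the one that the 2 x 2 calculation leaves out.

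A reader might also infer that the stated power does not apply at all. That goes too far. The G*Power figure does apply to group-by-visit, and the GLIMMPSE calculation is aimed at the cortisol response; its contrast may have been the three-way term, which the article neither shows nor excludes. Nor can one general power be quoted for the three-way test: step 3 of the working shows that it depends on the shape of the effect and can exceed 80% for a peak effect.

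Two smaller points also stand. On a per-visit summary of the response, such as an increase or an area under the curve, group-by-visit would be a response contrast; the article states no such summary. And a pre/post mixed model without baseline adjustment is valid. Adjustment gains precision; it does not correct an error.

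**Conclusion.** The point holds as a badly fixed choice of primary test. Type I error for the primary outcome is up to 9.75% if either interaction counts, and 5% if only the three-way term was meant, which is not stated. Applied to the individual samples and averaged over timepoints, group-by-visit can be positive from a basal shift alone. The 80% from G*Power is confirmed (80.7%, assuming a between-visit correlation of 0.5) for the two-way test and does not carry over to the three-way term; what the GLIMMPSE figure covers cannot be determined from the article.

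The error figure rests on the either-counts rule and near-independence of the two tests, which the simulation supports. The power contrasts rest on assumed effect shapes and correlations. This should be changed before unblinding; it does not make the design invalid.

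**What to change.** Before unblinding, name one decisive test for salivary cortisol. The preferred choice is a one-degree-of-freedom comparison of the arms on the post-intervention cortisol response, for example area under the curve with respect to increase over the eight samples, adjusted for the same measure at the baseline visit. The equivalent contrast in the mixed model, with baseline-visit means constrained equal across arms, would also serve. Report group-by-visit and group-by-visit-by-timepoint as supportive, and state which test each of the two power calculations covers, including the GLIMMPSE contrast.

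This is a change of wording and needs no new data. It holds type I error at 5% and matches the test to the stated outcome. The cost is that a pure shift in mean cortisol level would no longer count as success on the primary outcome. If the sponsor prefers to keep both interactions as principal, testing each at 0.025 also controls the error, at the price in power and completers shown in step 2 of the working.
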